## Abstract

**Background:**

Healthcare overuse, including unnecessary diagnostic testing and procedures, contributes to patient harm, increased healthcare costs, and resource waste. The Choosing Wisely initiative aims to reduce low‐value care through evidence‐based recommendations. However, limited evidence exists regarding the safety and effectiveness of implementing Choosing Wisely recommendations in intensive care settings.

**Methods:**

The WICH‐ICU is a registry‐based stepped‐wedge cluster randomized controlled trial designed to evaluate the implementation of specific Choosing Wisely interventions in Swedish intensive care units (ICUs). The study will include adult patients treated in participating Swedish ICUs. The intervention consists of three parts of the Choosing Wisely recommendations: (1) reduced frequency of arterial blood gas sampling, (2) reduced routine laboratory testing, and (3) reduced routine chest radiography. The primary outcome is 30‐day mortality. Secondary outcomes include ICU length of stay, duration of mechanical ventilation (invasive and noninvasive), continuous renal replacement therapy duration, and ICU readmission within 72 h. Intervention data, testing intensity (arterial blood gas samples, laboratory tests, and chest radiographs per patient‐day), will be collected through local monitoring, while outcome data will be obtained from the Swedish Intensive Care Registry (SIR). The stepped‐wedge design allows each participating ICU to serve as its own control, with randomized timing of intervention implementation.

**Discussion:**

This study will provide evidence on the safety and effectiveness of implementing Choosing Wisely recommendations in intensive care settings. The stepped‐wedge cluster randomized design minimizes contamination while allowing all participating sites to eventually receive the intervention. The results will inform evidence‐based de‐implementation strategies in critical care.

**Trial Registration:**

ClinicalTrials.gov identifier: NCT07013175

## Background

1

Healthcare systems worldwide face mounting pressure to optimize resource utilization while maintaining high‐quality patient care. Healthcare overuse—defined as the provision of medical services when the potential for harm exceeds the potential for benefit—represents a significant challenge in modern medicine [1]. This phenomenon is particularly pronounced in intensive care units (ICUs), where the critical nature of patient conditions often drives defensive medicine practices and the routine ordering of diagnostic tests and procedures [2, 3].

The Choosing Wisely (CW) initiative, launched in 2012 by the American Board of Internal Medicine Foundation, represents a physician‐led effort to advance conversations between clinicians and patients about avoiding unnecessary medical tests, treatments, and procedures [4, 5]. The initiative has since expanded globally, with professional societies developing evidence‐based recommendations to reduce low‐value care [6]. However, despite widespread adoption of CW recommendations, implementation in clinical practice remains challenging, particularly in high‐acuity settings such as ICUs [7].

### Rationale for CW in Intensive Care

1.1

ICUs are characterized by high resource utilization, complex patient populations, and frequent diagnostic testing [8, 9]. Several factors contribute to potential overuse in ICU settings:

*Defensive medicine practices*: The critical nature of ICU patients often leads to overcautious approaches, including frequent laboratory testing and imaging studies [10].
*Routine ordering packages*: Many ICU protocols include standing orders for daily laboratory tests and imaging studies, regardless of clinical indications [11].
*Shift‐based care*: The 24‐h nature of ICU care, with multiple handoffs between providers, may contribute to redundant testing [12].
*Technological availability*: The immediate availability of diagnostic technologies in ICU settings may lower the threshold for ordering tests [13].

### Evidence for CW Interventions in Critical Care

1.2

Several CW recommendations specifically target intensive care practices:

*Arterial blood gas (ABG) sampling*: Routine ABG sampling in stable ICU patients may not improve clinical outcomes while contributing to iatrogenic anemia through cumulative diagnostic blood loss, and increasing healthcare resource use and the risk of complications; in patients without indwelling arterial access it also causes avoidable discomfort [14]. Evidence suggests that stable patients on mechanical ventilation may not require hourly ABG sampling, with extended intervals being safe and cost‐effective [15].

*Laboratory testing*: Daily routine laboratory testing in stable ICU patients has been questioned, with studies suggesting that selective testing based on clinical indication may be equally safe while reducing costs and iatrogenic anemia [16, 17]. The Society of Critical Care Medicine has specifically recommended against daily laboratory testing in stable ICU patients [18].

*Chest radiography*: Daily routine chest x‐rays in ICU patients, particularly those on mechanical ventilation, have limited diagnostic yield and may not improve clinical outcomes [19, 20]. Multiple professional societies recommend against routine daily chest radiography in favor of clinically indicated imaging [18, 21].

### Knowledge Gaps and Study Rationale

1.3

Despite theoretical benefits and professional society recommendations, several knowledge gaps exist regarding CW implementation in intensive care:

*Safety concerns*: Limited high‐quality evidence exists regarding the safety of reducing diagnostic testing frequency in ICU patients [22].
*Implementation strategies*: Effective methods for implementing CW recommendations in ICU settings remain poorly understood [23].
*Patient outcomes*: The impact of CW interventions on patient‐centered outcomes in critical care requires further investigation [24].
*Healthcare utilization*: The broader effects of CW implementation on ICU resource utilization and efficiency need evaluation [25].
*Environmental impact*: The environmental impact of CW interventions in an ICU setting is unclear [26].

### Swedish Healthcare Context

1.4

Sweden's tax‐funded public healthcare system, characterized by universal coverage and integrated delivery systems, provides an ideal setting for evaluating the systematic implementation of CW interventions. The Swedish Intensive Care Registry (SIR), established in 2001, captures comprehensive data on all ICU admissions nationwide, enabling robust outcome assessment [27]. The registry's high coverage rate (> 95% of Swedish ICU beds) and standardized data collection procedures facilitate large‐scale implementation research [28, 29].

Swedish ICU practice patterns align with international standards, with similar approaches to diagnostic testing and monitoring. However, regional variations exist in practice, providing natural variation for studying implementation effects [30, 31].

## Objectives

2

### Primary Objective

2.1

To evaluate the safety and effectiveness of implementing specific CW interventions in Swedish ICUs by assessing whether they are non‐inferior to usual care with regards to 30‐day mortality.

### Secondary Objectives

2.2

To assess the impact of CW interventions on ICU length of stay.To evaluate effects on invasive mechanical ventilation duration.To evaluate effects on noninvasive mechanical ventilation duration.To evaluate effects on continuous renal replacement therapy duration.To evaluate effects on unplanned readmission.To analyze changes in diagnostic testing patterns and healthcare resource utilization.To analyze environmental impact.

### Hypotheses

2.3

We hypothesize that the implementation of targeted CW interventions in Swedish ICUs will:
Reduce diagnostic testing frequency without compromising patient safety.Maintain non‐inferior clinical outcomes while improving resource efficiency.Be feasible to implement across diverse ICU settings.Reduce resource use and environmental impact without negatively impacting quality indicators, such as ICU length of stay and unplanned ICU readmission within 72 h.

### Trial Registration

2.4

ClinicalTrials.gov identifier: NCT07013175 (first posted on June 17, 2025; last updated on November 21, 2025).

### Trial Status

2.5

Protocol version [2.0], dated August 8, 2026; version 1.0 dated November 24, 2025.

Recruitment opened on November 3, 2025 and is scheduled to close on November 30, 2026. The trial is registered at ClinicalTrials.gov (NCT07013175, https://clinicaltrials.gov/study/NCT07013175), first posted on June 17, 2025. This publication constitutes both the trial protocol and the statistical analysis plan; the full versions of both documents are deposited with the trial registration record and are available from the corresponding author on request. Results will be reported in a peer‐reviewed publication regardless of the direction of the findings, posted to the trial registry, and communicated to the participating ICUs and the wider Swedish intensive care community through SIR and SFAI. Authorship of trial publications follows ICMJE criteria; no professional medical writers were engaged. Cluster randomization and the design described here were finalized before recruitment opened; version 1.0 of the written protocol was filed on November 24, 2025. Version 2.0 differed from version 1.0 in the addition of a prespecified fidelity threshold for interpreting the primary result, a quantitative trigger for safety review, and expanded reporting of trial oversight and open‐science provisions. Version 3.0, prepared in response to peer review, adds a prespecified analysis model for the testing‐intensity outcomes, a per‐protocol analysis of the primary outcome reported alongside the intention‐to‐treat analysis, a hierarchical rule subordinating testing‐intensity and environmental outcomes to the primary safety outcome, and a contemporaneous comparison with nonparticipating SIR units. In no version have changes been made to eligibility, the intervention, the primary outcome, the non‐inferiority margin, or the primary analysis model. All versions were finalized before any outcome data were extracted or examined.

One participating unit, a small cardiothoracic ICU, withdrew from the trial on November 5, 2025, after cluster randomization and before the first clusters transitioned into intervention. Thirty‐seven units comprising 36 clusters therefore contributed data. The randomization sequence and the power calculation reported below are those prespecified for the 38 units (37 clusters) randomized; the withdrawal reduces the projected number of care episodes by approximately 197 (0.9%), so no recalculated power analysis will be done. The withdrawal and its timing will be shown in the CONSORT flow diagram of the primary‐results publication.

## Methods

3

### Study Design

3.1

WICH‐ICU is a registry‐based stepped‐wedge cluster randomized controlled trial [32]. We will roll out the intervention in 37 clusters (36 following the withdrawal of one unit after randomization; see Section 2.5). In all clusters, there will be a standard care phase and an implementation—intervention phase for a total of 13 months. The duration of each phase is determined by the randomized implementation sequence, but the standard care phase will be at least 1 month in all clusters. In this trial, clusters will be randomized to 1 of the 10 implementation sequences, meaning that three to four clusters will be randomized to each sequence (Figure 1). The schedule of enrollment, interventions, and assessments is shown in Table 1.

**FIGURE 1 aas70339-fig-0001:**
[figure not shown]
Randomization schedule.

**TABLE 1 aas70339-tbl-0001:** Schedule of enrollment, interventions, and assessments (SPIRIT table).

	Baseline/Enrollment	Control period (Standard Care)	Intervention period (Choosing Wisely)
Timepoint	November 2025	December 2025–September 2026 (Months 1–10; varies by cluster)	December 2025–November 2026 (Months 1–13; varies by cluster)
Enrollment			
Cluster eligibility assessment	X		
Cluster randomization to sequence	X		
Patient eligibility (continuous)		X	X
Notification of cluster transition			X (6–8 weeks prior)
Interventions			
Standard care period	X	X	
*Choosing Wisely bundle*			
ABG protocol			X
Laboratory protocol			X
Chest x‐ray protocol			X
Assessments			
Diagnostic testing patterns (ABGs, laboratory tests and chest x‐rays)	X	X	X
Baseline characteristics (SAPS3)	X	X	X
Primary outcome	X	X	X
30‐day mortality	X	X	X
Secondary outcomes	X	X	X
ICU length of stay	X	X	X
Mechanical ventilation duration	X	X	X
Duration of CRRT	X	X	X
Number of unplanned (within 72 h) readmissions	X	X	X
Environmental impact	X	X	X

The stepped‐wedge design was selected for several reasons:

*Ethical considerations*: All participating sites eventually receive the intervention, addressing ethical concerns about withholding potentially beneficial interventions.
*Pragmatic implementation*: The design allows for staged implementation, facilitating training and resource allocation.
*Statistical efficiency*: Each cluster serves as its own control, increasing statistical power.
*Contamination minimization*: The temporal separation reduces the risk of contamination between the intervention and the control treatment.

### Patient and Public Involvement

3.2

Patients and members of the public were not involved in setting the research question, designing the trial, or selecting the outcome measures. The intervention operates at the level of unit‐wide testing defaults rather than individual treatment decisions, no patient‐level recruitment or consent procedure exists, and all outcomes are ascertained from routinely collected registry data; the scope for meaningful individual‐level involvement in trial conduct was therefore limited. The choice of outcomes was nonetheless informed by patient‐relevant considerations: reduced iatrogenic anemia from cumulative diagnostic blood loss, reduced discomfort from repeated arterial punctures in patients without indwelling arterial lines, and reduced radiation exposure are among the documented benefits of the intervention, and the safety outcomes were selected as those a patient would care most about. Trial results will be disseminated to the public through SIR's and SFAI's public‐facing channels and through a plain‐language summary posted with the trial registration.

### Setting and Participants

3.3

#### Participating Sites

3.3.1

The study will be conducted in Swedish ICUs participating in the SIR. Eligible ICUs must:
Have > 95% data completenessTreat adult patients (≥ 18 years)Have committed local leadership supportDesignate a clinical monitor for data collection

#### Patient Population

3.3.2

All adult patients (≥ 18 years) admitted to participating ICUs during the study period will be included in outcome analyses. To account for the gradual onset of the treatment effect following the transition of each cluster from control to intervention, patients admitted within the first hour after the transition will be excluded from the analysis. No individual patient consent is required due to the registry‐based design and quality improvement nature of the interventions.

### Recruitment

3.4

We approached all Swedish ICUs via SIR and SFAI (Svensk Förening för Anestesi och Intensivvård: the Swedish society for anesthesia and intensive care) using both their web pages and their email lists. ICUs were excluded if they had fully implemented the targeted CW recommendations since such units could not contribute a valid standard‐of‐care control period, or if they declined participation. The 38 units (37 clusters) randomized cover approximately 53% of all adult ICU admissions in Sweden; following the withdrawal of one small cardiothoracic unit after randomization, 37 units (36 clusters) contribute data, with coverage unchanged at approximately 53%. Individual patients are not recruited: all care episodes in participating units are identified through routine SIR registration, capturing over 95% of all Swedish ICU admissions using standardized definitions, and outcomes are ascertained by the registry. This registry‐based mechanism removes the risk of selective enrollment and is the reason no patient‐level recruitment procedures are required.

### Intervention Bundle

3.5

The WICH‐ICU intervention consists of a bundle of three evidence‐based CW recommendations:
ABG Sampling Protocol

*Current practice*: Routine hourly ABG sampling in many ICUs.

*Intervention*: Structured protocol for ABG frequency:

*Hourly sampling*: Unstable patients where results directly change treatment.
*Every 2 h*: Unstable patients where results may not immediately change management.
*Every 4 h*: Stable patients where results may change management.
*Less frequently than every 4 h*: Stable patients where results are unlikely to change management.
2Blood test Protocol

*Current practice*: Daily routine laboratory panels regardless of clinical status.

*Intervention*: Risk‐stratified laboratory testing approach:

*Daily testing*: Essential parameters (e.g., albumin, blood count, CRP, and creatinine)
*Every other day/twice weekly*: Intermediate priority tests (e.g., liver enzymes, coagulation studies, electrolytes, and procalcitonin)
*Avoid routine testing*: Low‐yield tests without specific clinical indication
3Chest Radiography Protocol

*Current practice*: Routine chest x‐rays after insertion of central venous lines, after insertion of nasogastric tubes, after initiation of invasive ventilation, and for many mechanically ventilated patients.

*Intervention*: Clinically indicated chest radiography only:
Chest x‐rays performed *only when diagnostic information would directly affect clinical management*.
○Examples of appropriate indications: suspected pneumothorax, line placement confirmation in “difficult” cases, acute respiratory deterioration.

### Modification and Discontinuation of the Intervention

3.6

Because the intervention operates at the cluster level and modifies testing defaults rather than restricting indicated care, clinically indicated testing at any frequency constitutes intended use of the protocols rather than a deviation and requires no justification beyond routine clinical records. No concomitant care is prohibited, and no co‐intervention is introduced: all treatment other than the frequency of routine, non‐indicated diagnostic testing continues according to local practice in both trial conditions. The protocol materials and decision‐support tools distributed to participating units are available from the corresponding author on request.

At the cluster level, the intervention may be paused or modified at a participating ICU if the monthly safety monitoring identifies a signal of harm at that unit, if local circumstances (e.g., a major surge in patient volume or a staffing crisis) make continued adherence unsafe or impracticable, or at the request of local clinical leadership. Decisions to pause, modify, or discontinue the intervention at a site are made by the principal investigator together with the steering committee, in consultation with the local investigator and, where a safety signal is involved, the safety review group. Any such decision, its rationale, its duration, and the affected periods are documented in the trial master file, reported in the trial publication, and handled in the per‐protocol sensitivity analysis.

### Implementation Strategy

3.7

#### Pre‐Implementation Phase

3.7.1

Baseline monitoring of current testing practicesStaff education and training sessionsDistribution of protocol materials and decision support toolsLocal champion identification and training

#### Implementation Phase

3.7.2

Phased rollout according to randomization schedule; all centers transitioning from control to intervention phase will be informed 6–8 weeks prior.Regular feedback on adherence and outcomes.Continuous quality improvement processes.

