#### Randomization Scheme

4.5.2

The 37 clusters were randomized to 1 of the 10 implementation sequences, with three or four clusters allocated per sequence; this restricted allocation ensures a balanced stepped‐wedge layout across the 13 monthly periods. The allocation sequence was generated by a constrained randomization algorithm implemented in R (version 4.6) with a fixed random seed. The seed, the generating script, and equivalent implementations in Stata and Python have been archived and will be made available with the trial report, allowing full reproduction of the allocation. Randomization was stratified by ICU category and ICU size (admissions/year). One prespecified constraint was applied: the two ICUs sharing staff at the same hospital were treated as a single cluster and therefore necessarily follow the same sequence. The sequence was created by [name], who had no clinical role at any participating unit. Because randomization was at the cluster level and no individual patient was enrolled, there were no enrolling personnel whose behavior could be influenced by foreknowledge of the next allocation, and conventional allocation concealment is not applicable in the individual‐participant sense. The generated sequence was not disclosed to participating units before allocation was complete; each cluster was subsequently informed of its own transition date 6–8 weeks in advance, as described above. The full allocation list is stored securely with the trial master file.

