### General Principles

5.1

Analysis of the primary outcome follows the intention‐to‐treat principle, with every care episode analyzed according to the randomized state of its cluster at the time of admission and irrespective of local adherence; a prespecified per‐protocol analysis is reported alongside it.Mixed‐effects models will account for clustering and temporal trends.Multiple imputation will address missing data when > 10% are missing for key covariates.Sensitivity analyses will explore the robustness of findings.Statistical significance will be set at *α* = 0.05 for superiority analyses and *α* = 0.025 (one‐sided) for non‐inferiority analyses.

No adjustment for multiplicity is made. Only the primary outcome supports a confirmatory conclusion; secondary, process, and exploratory outcomes are reported as point estimates with 95% confidence intervals (CIs) and interpreted as supportive, with no formal non‐inferiority testing applied to them.

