Because the estimand is an absolute risk difference, adjusted marginal risks under intervention and control are obtained from the fitted model by regression standardization (g‐computation): the model is used to predict each episode's outcome probability under both treatment conditions, and these predictions are averaged over the trial population. The adjusted risk difference is the difference between the two standardized risks, with a 95% CI obtained by cluster bootstrap or delta method. Non‐inferiority is declared if the upper bound of the two‐sided 95% CI (equivalently the one‐sided 97.5% bound) for the adjusted risk difference (intervention minus control) lies below 3 percentage points. Intention‐to‐treat analysis behaves differently in a non‐inferiority trial than in a superiority trial. Whereas incomplete adherence biases a superiority comparison toward the null and is therefore conservative, in a non‐inferiority comparison it makes the two conditions more alike and so makes a conclusion of non‐inferiority easier to reach; intention‐to‐treat is in this sense anti‐conservative [37]. We therefore prespecify a per‐protocol analysis alongside the primary intention‐to‐treat analysis. The per‐protocol population comprises all control periods together with those intervention cluster‐periods in which the cluster's own testing intensity met the fidelity criterion; cluster‐periods during which the intervention was paused or modified under the provisions above are excluded from the intervention condition. The per‐protocol analysis uses the same model, covariates, and non‐inferiority margin as the primary analysis. A conclusion of non‐inferiority requires the upper confidence bound to lie below the margin in both analyses. Where the two are discordant, both are reported, and the discordance is discussed rather than resolved by rule. Realized testing intensity is reported for both conditions at cluster level so that the separation achieved is visible to the reader.

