### Sensitivity Analyses

5.5

*Time trend specifications*: Alternative modeling of temporal trends.
*Outlier ICUs*: To assess the influence of potentially outlying clusters, a binary indicator variable identifying these clusters will be included in the model both as a main effect and in interaction with treatment.
*Baseline period*: Varying length of baseline observation period.
*Minimal detectable difference*: Minimal detectable difference will be calculated to evaluate the assumptions of power analysis.To assess for the gradual onset of the treatment effect following each cluster's transition from control to intervention, the treatment variable will be replaced by a categorical variable with the following levels: “Before switch,” “0–7 days after switch,” “8–14 days after switch,” and “> 14 days after switch.”If ICU drop‐out or wrongful randomizations occur, a per‐protocol analysis will be performed to account for this.Contemporaneous external comparison: Because SIR captures over 95% of Swedish ICU admissions, admissions to nonparticipating Swedish ICUs over the same calendar months provide a contemporaneous, non‐randomized external comparison. Risk‐adjusted 30‐day mortality is compared between participating and nonparticipating units by calendar period, adjusted for SAPS 3, age, sex, admission type, and ICU category, to characterize secular trend and background fluctuation in mortality unrelated to the intervention and to provide an indirect check for diffusion of CW practice beyond the trial. Because participation was not randomly assigned and participating units differ from nonparticipating units in size, category, and case mix, this comparison is descriptive and is not interpreted as an effect estimate.

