Several limitations warrant consideration. Secular trends may confound intervention effects, although calendar time is modeled explicitly; registry data may not capture all relevant confounders; local implementation may vary between sites; and knowledge of the intervention could influence practice during control periods. As a single‐country study, the results may not fully generalize to healthcare systems with different practice patterns, culture, or resources.

Beyond patient safety and resource use, the trial will quantify the environmental impact of reducing low‐value testing, contributing to an emerging evidence base that links CW to healthcare sustainability [26, 40]. The trial does not undertake a formal health‐economic evaluation, and we make no claim about monetary savings. Most of the short‐run cost of a blood gas, a laboratory panel or a chest radiograph is staff time and installed capacity, both fixed over the horizon of this trial; reduced test volume does not become reduced expenditure unless that capacity is redeployed, and internal cross‐charging between clinical and service departments can offset an apparent saving within the same system. Reductions in testing are therefore reported in natural units and should not be read as realized savings. The environmental outcome is less exposed to this argument, since avoided consumables, reagents, and their transport are variable inputs whose emissions are avoided directly, and it is for this reason that CO_2_e rather than cost is reported as the efficiency‐side outcome. If non‐inferiority is demonstrated, the results will support evidence‐based de‐implementation of low‐value ICU diagnostics, and the design may serve as a model for similar evaluations in other settings and clinical areas.

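### The 6–8 weeks between notification and the switch count as ordinary control time in every mortality analysis, so early adoption, if it occurs, would pull the result towards non-inferiority unseen

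*Protocol article*

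**What the plan says.** **Notice.** Section 3.7.2 states that "all centers transitioning from control to intervention phase will be informed 6–8 weeks prior". Randomization Scheme (4.5.2) confirms it for every unit: "each cluster was subsequently informed of its own transition date 6–8 weeks in advance". Section 3.7.1 lists staff education, distribution of protocol materials and decision-support tools, and champion training as pre-implementation steps. It gives no dates for them.

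**Length of control.** Study Design (3.1) says that "the standard care phase will be at least 1 month in all clusters". Table 1 gives a control period of months 1–10, varying by cluster.

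**Classification.**
- Primary analysis (5.1): "every care episode analyzed according to the randomized state of its cluster at the time of admission".
- Exclusion around the switch (3.3.2): "patients admitted within the first hour after the transition will be excluded from the analysis". It acts only after the switch.
- Per-protocol set (5.2): "The per‐protocol population comprises all control periods together with those intervention cluster‐periods" that met the fidelity criterion.
- Onset analysis (5.5): "the treatment variable will be replaced by a categorical variable with the following levels", of which three lie after the switch and one covers all time before it.

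**Acknowledgement.** The limitations in the Discussion concede that "knowledge of the intervention could influence practice during control periods". No analysis is attached to that sentence.

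**The concern.** Section 5.2 itself explains that whatever makes the two conditions more alike makes non-inferiority easier to reach, and it adds a per-protocol analysis for that reason. That remedy removes low-fidelity time only from the intervention side. The same likeness could arise on the control side, if a unit that knows its date and has been trained starts to cut routine testing before the switch. The onset analysis looks for a gradual effect only after the switch, so it cannot show an effect that begins before it.

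At stake is the error that matters most here: declaring non-inferiority on 30-day mortality when the true excess is at the margin. Time close to the switch carries much weight in a within-cluster, period-adjusted contrast, so the loss can exceed the simple share of control time affected.

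**Working it through.** **Inputs from the article.** 37 clusters, 10 sequences of three or four clusters, 13 monthly periods, 47 admissions per cluster-period, ICC 0.009, baseline mortality 18%, margin 3 points, one-sided alpha 0.025, stated power 89% (sections 3.1 and 4.4.2); notice of 6–8 weeks.

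**Assumptions.** Switches fall at the start of months 2 to 11, so control lasts 1 to 10 months. The model is linear on cluster-period means, with a random cluster intercept and categorical periods, as an approximation to the planned logistic mixed model. The fraction *a* of the effect already present in the notified weeks is assumed, because the article gives none.

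**Step 1: the stated power.** Power = Φ(3/SE − 1.96), SE in percentage points.
- Binomial variance at 21%: SE = 0.934, and Φ(3.212 − 1.96) = 89.5%, which matches the stated 89%.
- Variance at 18%: SE = 0.881, and Φ(3.405 − 1.96) = 92.6%.

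Both SEs are carried forward.

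**Step 2: share of control time after notification.** Six weeks is 1.38 months and eight weeks is 1.84. Share = Σ min(control months, notice) / Σ control months. With equal sequences the denominator is 1 + 2 + … + 10 = 55.
- 6 weeks: (1 + 9 × 1.38)/55 = 13.42/55 = 24.4%.
- 8 weeks: (1 + 9 × 1.84)/55 = 17.56/55 = 31.9%.

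Over all placements of the three-cluster sequences, the ranges are 23–26% and 31–34%. If switches ran from month 3 to 12 the share would be about 20–30%; from month 4 to 13, about 18–26%. A sequence with one month of control would be notified for all of it. With two months it would be notified for 1.38/2 = 69% to 1.84/2 = 92%.

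**Step 3: dilution.** The expected treatment coefficient was computed with effect *a* in the notified weeks and 1 after the switch. *r* is the ratio of the expected estimate to the true effect.

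**Step 4: false non-inferiority at a true excess of 3 points.** P = Φ(3(1 − r)/SE − 1.96). For example, with *r* = 0.669 and SE = 0.881: 3 × 0.331/0.881 = 1.127, and Φ(−0.833) = 20.2%.

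| *a* | notice | *r* | expected estimate (points) | P, SE 0.881 | P, SE 0.934 |
|---|---|---|---|---|---|
| 0 | either | 1.00 | 3.00 | 2.5% | 2.5% |
| 0.25 | 6 weeks | 0.869 | 2.61 | 6.5% | 6.2% |
| 0.25 | 8 weeks | 0.834 | 2.50 | 8.1% | 7.7% |
| 0.50 | 6 weeks | 0.738 | 2.21 | 14.3% | 13.2% |
| 0.50 | 8 weeks | 0.669 | 2.01 | 20.3% | 18.5% |

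A layout one month later gives nearly the same *r* (0.83–0.87 at 25%, 0.66–0.73 at 50%).

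**Step 5: precision of the proposed contrast.** Giving the notified weeks their own coefficient raises the SE of intervention against un-notified control from about 0.88 to 1.07–1.12 points.

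**The case against.** **Notice is not adoption.** Being told a date is not the same as changing practice, and undated training need not fill the window. A reader might infer that control time *is* contaminated and harm *is* diluted. The article does not support that: it says nothing about early adoption, and at *a* = 0 the bias is zero. The error rates also assume a true excess of exactly 3 points, which section 4.4.1 considers implausible. This objection stands, so the point is conditional.

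**Classification by randomized state is correct.** Under a treatment-policy estimand it is the right primary rule, and staged rollout needs notice. This also stands; neither should change.

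**Un-notified time is not perfectly clean.** Units volunteered with committed leadership, so some awareness predates notification. That limits the added contrast without making it uninformative.

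**Safeguards exist.** Continuous electronic record data where available, consumables orders by cluster-period, and cluster-level reporting of testing intensity could show drift before the switch. Section 5.5 also plans to vary the baseline length, without naming the notified window. None of these is a mortality analysis that separates these weeks.

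**The fidelity criterion.** A reader might infer that a baseline window falling within the notified weeks weakens the 5% criterion. The direction is the reverse: a lowered baseline shrinks the measured reduction and makes the threshold harder to meet, so an inconclusive report becomes more likely. An un-notified reference would credit more separation than the primary contrast contains. The criterion is therefore a partial protection.

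**A fuller plan may exist.** Section 2.5 presents the article as both protocol and analysis plan, with full versions deposited that are not shown here. Since section 5.5 fixes the onset categories explicitly, the suggestion amends a stated analysis.

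**Conclusion.** The gap is real and modest: the notified weeks are pooled with all other control time in the primary, per-protocol and onset analyses, and any early adoption would act in the direction that favours the trial's claim. The affected share is about a quarter to a third of control cluster-time under the layout implied by the text, and about 18–30% under later layouts. The size of the bias depends wholly on an unstated adoption fraction: none at zero, a loss of about 13–17% of the effect at 25%, and about 26–33% at 50%. These figures rest on the assumed layout and a linear approximation. They show that the question deserves an analysis; they do not show that the primary result will be biased.

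**What to change.** In the onset analysis of section 5.5, replace the single pre-switch level with two: more than 8 weeks before the switch, and 0–8 weeks before it. Where notification dates are recorded, split at the cluster's own date instead. Take the un-notified level as reference. With the post-switch levels pooled, report the adjusted risk difference of intervention against un-notified control, with its 95% confidence interval, beside the primary result as a prespecified sensitivity analysis. Use the planned electronic record and consumables data to report testing intensity in the notified weeks, so that readers can judge whether early adoption took place. Leave the primary analysis, the margin and the fidelity reference as they are.

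The cost is one more model on data already planned, plus an amendment under section 6.2, since it changes the analysis plan. It should be fixed before outcome data are extracted. The added contrast is less precise (SE about 1.07–1.12 against 0.88 points), and the earliest sequences contribute little or no un-notified control time. Dropping the window from the primary analysis would be disproportionate: setting aside one control month per cluster leaves power of about 81–85%, and two months about 71–76%, below the article's own 80% floor.
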